### **12.3.2. Data Management Procedures and Data Verification**

Designated personnel using the electronic CRF will have access based on their specific roles in the protocol. Please specify them here.

Completeness of entered data will be checked automatically by the eCRF system, and users will be alerted to the presence of data inconsistencies. Additionally, the Study Coordinator and CTA will cross-reference the data to verify accuracy. Missing or implausible data will be highlighted for the PI requiring appropriate responses (i.e. confirmation of data, correction of data, completion or confirmation that data is not available, etc.).

The database will be reviewed and discussed prior to database closure, and will be closed only after resolution of all remaining queries. An audit trail will be kept of all subsequent changes to the data.

### **12.3.3. Study Closure**

Following completion of the studies, the PI will be responsible for ensuring the following activities:

- Data clarification and/or resolution
- Accounting, reconciliation, and destruction/return of used and unused study drugs, if applicable
- Review of site study records for completeness
- Shipment of all remaining laboratory samples to the designated laboratories.

## **13 STATISTICAL METHODS AND DATA ANALYSIS**

All statistical analysis will be performed under the direction of the statistician designated in key personnel. Any data analysis carried out independently by the investigator must be approved by the statistician before publication or presentation.

### **13.1 Primary Objective**

1. The primary study outcome is comparison of 30-day continuous biochemically confirmed abstinence at 12-weeks post-TQD in participants randomized to adaptive pharmacotherapy algorithm vs. standard-of-care treatment. This will be confirmed by carbon monoxide breath testing with CO < 7 ppm.

### **13.2 Secondary Objectives**

2. To compare 7-day point prevalent biochemically confirmed abstinence rates at 2- and 12-weeks post-TQD in participants randomized to adaptive pharmacotherapy vs. standard-of-care treatment (Varenicline/Nicotine patch).
3. To compare phone-assessed self-reported abstinence at 1, 2, 6, 12, 26 and 52 weeks post-TQD in participants randomized to adaptive vs standard treatment. Phone assessments will be compared at specific time points and also across multiple time points using multi-level modeling.
4. To compare smoking reduction (number of cigarettes per day) at 2 and 12 weeks post TQD in participants randomized to adaptive vs standard treatment.
5. To compare smoking reduction (number of cigarettes per day) on phone-based self-report at 1, 2, 6, 12, 26, and 52 weeks post-TQD in participants randomized to adaptive vs. standard treatment. Phone assessments will be compared at specific time points and also across multiple time points using multi-level modeling.

### 13.3 Handling of missing values, censoring, and discontinuations

An intent-to-treat approach will be taken in which any subjects lost to follow-up after the point of randomization will be counted as non-abstinent. In addition, a sensitivity analysis will be conducted to determine the impact of “missingness” and smoking at previously observed time-points.

### 13.4 Statistical Hypothesis, Model, and Method of Analysis

Outcomes will be analyzed using generalized linear regression modeling using an ANOVA-based design; randomization status to both pharmacotherapy and behavioral groups will be denoted using a proxy variable to test primary study effects. An alpha criterion of 0.05 (two-tailed) will be used in all comparisons.

**Data Management and Statistical Procedures:** All data measures collected during study visits (e.g., smoking history, demographics, standardized tests on nicotine dependence, anxiety, stress etc.) will be captured in the EMR. Phone-based data will be captured using REDCap, an encrypted, HIPAA compliant, Duke Translational Medicine Institute (DTMI)-based data collection system allowing for multi-site data entry, direct participant electronic data upload through interface with computer terminals or tablets, time-based data entry (for use in calendar-based Assessment Visits) and capacity for direct upload into statistical programs SAS, SPSS, R, Excel for analysis. Trained staff (Duke CITI certification) will conduct data integrity processes for REDCap data with download into SAS (SAS Institute, Cary NC).

**Multilevel Modeling:** Given repeated observations across multiple individuals, many of the analyses in this study will be derived from multilevel modeling (MLM). MLM models hierarchically organized data, in which data at the lowest level of the analysis (e.g., measured at a given time point) can be modeled as a function of time point-specific (Level 1) variables and person-specific variables (Level 2). Unlike repeated-measures ANOVA, MLM is able to also handle imbalanced data with unequal variances across clusters/individuals (Searle S., 1992). In addition to modeling between-person differences in momentary levels of an outcome variable (MLM with intercepts as outcome), MLM is also able to model individual differences in changes in momentary outcomes over time (MLM with intercepts and slopes as outcomes), also known as latent-growth curve modeling. Because MLM procedures are based on maximum likelihood estimation and use all available data, MLM can accommodate data missing at random and is often considered favorable to multiple imputation techniques, which can yield results that vary substantially depending on the imputation model and iteration (D, 2012; L & K, 1998). Nevertheless, missing data will be examined to determine whether missingness is systematic (i.e., associated with individual baseline differences or time-related changes in observed variables). An intent-to-treat approach in which subjects lost to follow-up will be counted as non-abstinent will also be used to analyze univariate outcomes. An alpha criterion of 0.05 (two-tailed) will be used in all comparisons.

**Analysis of Primary Outcome:** The primary outcome measure is biochemically confirmed 30-day continuous abstinence at the 12-week post-Target Quit Day (TQD) confirmed by carbon monoxide (CO) breath testing with CO < 7ppm. The study hypothesis is that adaptive treatment arms of the study will show higher smoking abstinence at 12-weeks post-quit attempt vs. non-adaptive treatment. An intent-to-treat approach will be taken to analyze primary outcomes such that all subjects who are enrolled in the study will be included in the primary analysis of outcomes. Outcomes will be analyzed using generalized linear regression modeling using an ANOVA-based design. An alpha criterion of 0.05 (two-tailed) will be used in all comparisons. For a conservative estimation of abstinence, subjects lost to follow-up after the point of randomization will be counted as non-abstinent. Following this, however, a sensitivity analysis will be conducted to determine the impact of this assumption, using multiple imputation procedures that model smoking outcomes in terms of “missingness” and smoking at previously observed time-points.

**Secondary smoking outcomes:** Analysis of secondary smoking outcomes will include comparison of abstinence rates in Adaptive vs. Non-Adaptive groups via self-reported 7 and 30-day continuous abstinence and number of cigarettes smoked per day at 2- and 12-weeks post TQD. Secondary smoking outcomes will be assessed using intent-to-treat principles with use of multiple imputation to account for missing data.

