## **3.2 Background and Significance**

**Adaptive Treatment Regimens:** The primary study treatment is a medication strategy referred to here as the adaptive pharmacotherapy algorithm. This strategy uses FDA-approved medications for smoking cessation (Varenicline, Nicotine Patch and Bupropion). Two weeks after starting these treatments, participants are assessed to see how much they have reduced their smoking on these medications. If, after 2 weeks of treatment, participants have reduced their cpd to 50% or less of baseline, they are considered to be “responsive” to treatment and are continued on this treatment alone until 12 weeks post-TQD. After 2 weeks of treatment, participants who have not decreased their cigarette use to 50% or more of their baseline cpd are considered “non-responders”, and Bupropion is added to the treatment regimen 2 weeks prior to the quit attempt and continued until 12 weeks post TQD. Estimates based on prior studies within our lab (see preliminary studies) suggest 50% will be non-responders.

**Pharmacotherapy Control:** The control group used for this algorithm is Varenicline started 1 week prior to TQD (1 week escalating dose) or Nicotine Patch started on the TQD and continuing to 12 weeks post-TQD. This is considered standard of care treatment. P-Varenicline and P-Patch for control participants only will be started 4 weeks prior to TQD, and P-Bupropion will be started 1 week prior to TQD to match study groups

**Behavioral Treatments:** All participants will receive one 40-minute visit with a medical provider who specializes in tobacco dependence treatment.

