### 3.6 Data Analysis and Statistical Considerations

**Detailed Data Analysis is provided in Section 13.** A summary of data analysis procedures includes the following: **Multilevel Modeling:** Given repeated observations across multiple individuals, many of the analyses in this study will be derived from multilevel modeling (MLM). **Missing Data:** Missing data will be examined to determine whether missingness is systematic (i.e., associated with individual baseline differences or time-related changes in observed variables). An intent-to-treat approach in which subjects lost to follow-up will be counted as non-abstinent will also be used to analyze univariate outcomes. An alpha criterion of 0.05 (two-tailed) will be used in all comparisons. **Analysis of Primary Outcome:** The primary study outcome is comparison of abstinence rates in adaptive vs standard treatment groups. The primary outcome measure is biochemically confirmed 30-day continuous abstinence at the 12-week post-quit attempt (carbon monoxide breath testing with CO < 7ppm). **Secondary abstinence outcomes:** Includes comparison of abstinence rates in adaptive vs standard treatment groups via self-reported 7 and 30-day continuous abstinence at 2- and 12-weeks post-TQD as well as phone-based self-reported abstinence at 1, 2, 6, 12, 26, and 52 weeks post-TQD. **Continuous Smoking Outcomes:** In addition to dichotomous outcomes described above, there will be an assessment of number of cpd and number of days abstinent at 2- and 12-week post TQD assessment visit (as well as phone assessment time points). **Assessment of potential moderators of primary effect:** The following constructs will be assessed as potential predictors of abstinence: demographics (age, gender, race, education), smoking history and heaviness, prior quit attempts, financial status, dependence (FTND), urge rating (MPSS), depression (PHQ-2), anxiety (GAD-2), alcohol use (AUDIT-C), stress (PSS-4), self-efficacy questions. **Assessment of potential mediators of primary effect:** The following constructs will be assessed to determine whether assignment to pharmacotherapy group is associated with change in these constructs pre- and post-treatment: urge rating (MPSS), depression (PHQ-2), anxiety (GAD-2), stress (PSS-4), self-efficacy. **Economic Analysis:** An economic analysis of the Algorithm vs. Standard treatment from multiple perspectives will be provided. **Sample Size Calculation:** Total sample size required to show differences on primary outcomes between pharmacotherapies and behavioral treatments with 10% downward adjustment in study group outcomes for possibility of unexpectedly poor outcomes is **N = 300**.

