| Secondary   | To compare smoking reduction (number of cpd) and on phone-based self-report at 1, 2, 6, 12, 26 and 52 weeks post-TQD in participants randomized to adaptive pharmacotherapy algorithm vs. standard-of-care treatment. Phone assessments will be compared at specific time points and also across multiple time points using multi-level modeling. | Self-reported abstinence rates via phone-based assessment at 24 hours post-TQD, 1-week post-TQD, 2-week post-TQD, 6-week post-TQD, 26-week post-TQD, and 52-week post-TQD.                                                                                                                                                                                                                                            | See Section 13 |
| Exploratory | To assess demographic variables (age, gender, race, education, and income) for an association with all abstinence outcomes and, if significant, will be used as covariates in analysis of all abstinence outcomes.                                                                                                                                | Self-reported demographic information assessed through surveys administered at the baseline visit.                                                                                                                                                                                                                                                                                                                    | See Section 13 |
| Exploratory | To assess potential baseline (pre-intervention) predictors of abstinence including self-reported dependence, stress, anxiety, depression, alcohol and drug use, and self-efficacy. If a baseline variable is found to be associated with abstinence, it will be further assessed as a moderator of abstinence.                                    | Self-reported baseline standardized measures on these psychological constructs assessed through surveys administered at the baseline visit.                                                                                                                                                                                                                                                                           | See Section 13 |

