#### 7.1.6. Randomization

Randomization will occur through an open source randomization program “Research Randomizer” developed for randomization of subjects in psychology and medication trials. This can be found at <https://www.randomizer.org/>. To simulate clinical treatment, the study design provides for subject choice into one of two arms: Varenicline-based treatment (n=150) or Nicotine Patch-based treatment (n=150). Once the initial treatment arm is chosen, subjects will be randomized to Varenicline adaptive pharmacotherapy (n=75) vs. Varenicline alone (n=75), or similarly nicotine patch adaptive treatment (n=75) vs. nicotine patch alone (n=75).

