**Varenicline-Based Treatment (secondary outcome):** Power calculation for Varenicline Based Adaptive treatment vs. Varenicline Standard Treatment is based on abstinence rates observed in prior P50-funded trials as well as other published studies. To estimate the effect of adaptive treatment, a critical consideration is that 4 week Varenicline pre-cessation treatment without adaptation was superior to starting 1 week prior to quit day (Hajek et al 2011). Abstinence rate were 20.8% 1-week pre-quit start time. Hajek further showed that for participants starting 4 weeks prior to the Quit day, 35.4% of participants showed >50% reduction in cigs/day with an abstinence rate of 66.7% whereas 64.6% of participants failed to show >50% reduction in cigs/day and had an abstinence rate of 22.6%. The weighted average of these groups = 38.2%. Sample size calculation using **38.2% vs. 20.8%** with 2-tail test with continuity correction assuming  $p = 0.05$  and power = 80%, yields a minimum sample size of **208** within the Varenicline arm alone. This study is designed with 150 in the Varenicline arm and so it underpowered to reach this secondary outcome.

Version Date: 02/26/2020

**Full Sample (Primary Outcome):** Based on these calculations, a sample size of 300 for each of these comparisons should be sufficient to demonstrate significant differences between randomized arms (150 vs. 150). The Primary Outcome is a comparison of 12-week post-TQD smoking abstinence across the study sample (N=300). As stated above, the nicotine patch arm will require n=298 to reach significance, and the varenicline arm will require n=208 to reach significance. Neither arm (150 each) is powered to reach significance. The two arms together (n=300) are powered to reach primary outcomes. For the control group (nicotine patch arm = 26.0%; varenicline arm = 20.8%), an equally weighted sample would result in an abstinence rate of **23.4%**. For the adaptive treatment group (nicotine patch arm = 41.2%; varenicline arm = 38.2%), an equally weighted sample would result in abstinence rate of **39.7%**. A sample size calculation using 2-tail test with continuity correction assuming  $p = 0.05$  and power = 80% results in sample size of **248**. With 300 participants this study as power of 87% power for showing significant results on our primary outcome.

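### The stated primary model includes a behavioral randomization the trial does not have, does not name the stratum it does have, and lets significance tests add covariates

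*Protocol*

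**What the plan says.** Section 13.4 (Statistical Hypothesis, Model, and Method of Analysis) gives the model class, "Outcomes will be analyzed using generalized linear regression modeling using an ANOVA-based design", and then its factors: "randomization status to both pharmacotherapy and behavioral groups will be denoted using a proxy variable to test primary study effects". The Analysis of Primary Outcome paragraph repeats the model class and names no factor, stratum or covariate. The synopsis (Section 3.6) carries the same behavioral reference into the sample size: "Total sample size required to show differences on primary outcomes between pharmacotherapies and behavioral treatments".

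The design sections describe something else. On behavioral treatment, Section 3.2 states: "All participants will receive one 40-minute visit with a medical provider who specializes in tobacco dependence treatment". On allocation, Section 7.1.6 states: "Once the initial treatment arm is chosen, subjects will be randomized to Varenicline adaptive pharmacotherapy (n=75) vs. Varenicline alone (n=75"), with the same 75:75 split for those who choose the patch.

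The Objectives and Endpoints table (Section 6) has an exploratory row in which age, gender, race, education and income are tested for association with all abstinence outcomes and, "if significant, will be used as covariates in analysis of all abstinence outcomes".

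**The concern.** The sentence that fixes the test of the primary effect should describe the trial's randomization. It names a factor that is the same for everyone and leaves out the one within which allocation takes place. A statistical analysis plan can add detail to a protocol sentence, but it could not add detail to this one without contradicting it.

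The covariate rule is a separate weakness. Taken literally, all abstinence outcomes include the primary one. The terms of the primary model would then depend on which demographics happen to correlate with abstinence in the trial's own data, and the model could not be written down before the outcome is known. What is at stake is a primary analysis that is fixed in advance and follows the randomization.

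**Working it through.** **1. Is there a behavioral factor?** Sections 3.1 and 3.2 give all participants the same 40-minute visit. Sections 3.3 and 7.1.6 randomize only adaptive versus standard. A behavioral-group variable therefore has one level. It is indistinguishable from the intercept and has no estimable coefficient. Software drops it, and the adaptive-versus-standard term is unaffected.

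**2. The plan's own figures.** Section 13.4 (Sample Size Calculation) pools the two medication groups: control (26.0 + 20.8)/2 = 23.4%, adaptive (41.2 + 38.2)/2 = 39.7%. Two-sided alpha is 0.05 and power 80%; the section states N = 248, and 87% power at N = 300.
- Unpooled variance, no continuity correction: n per arm = (1.960 + 0.842)² × (0.397×0.603 + 0.234×0.766) / 0.163² = 7.849 × 0.4186 / 0.02657 = 123.7, so 124 per arm and 248 in total.
- Power at 150 per arm: 0.163 / √(0.4186/150) − 1.960 = 3.085 − 1.960 = 1.125, giving 87.0%.

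Both figures reproduce. The section says a continuity correction was used. With one, the results are 278 and 83.4%. That is a separate matter, and N = 300 still exceeds 80% power.

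**3. Effect of the stratum term.** This step uses the usual test with pooled variance under the null, and 75 per cell.
- Unstratified: (0.163 − 1.960×√(2×0.3155×0.6845/150)) / √(0.4186/150) = (0.163 − 0.1052)/0.0528 = 1.095, giving 86.3%.
- Stratified by chosen medication (Mantel-Haenszel weights, differences 0.152 and 0.174): (0.163 − 1.960×0.0536)/0.0528 = 1.098, giving 86.4%.
- Logistic simulation at the same rates: power 86.7% without and 86.8% with the term (3,000 trials); type I error 5.1% and 5.3% (4,000 trials, Monte Carlo standard error √(0.05×0.95/4000) = 0.3 points).

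Participants choose their medication, so an equal split is not guaranteed. The stratified power is 83.3% at 225 patch / 75 varenicline and 89.1% at the reverse.

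**4. Effect of the significance rule.** If five unrelated demographics are each screened at 5%, at least one enters with probability 1 − 0.95⁵ = 22.6%. Simulated type I error of the treatment test after screening (five independent covariates, 4,000 trials):

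| Covariate effect | Selected model reported | Better of unadjusted and selected |
|---|---|---|
| None | 5.2% | 5.4% |
| Log-odds 0.3 each (assumed) | 5.1% | 6.1% |

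**5. What a prespecified baseline covariate could add.** The protocol gives no effect size for any baseline variable, so a range is assumed. The simulation (4,000 trials) used 41.0% for the adaptive patch group; the Nicotine Patch paragraph contains both 41.0% and 41.2%.

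| Assumed odds ratio per SD | Unadjusted | Stratum | Stratum + covariate |
|---|---|---|---|
| 1.0 | 85.6% | 85.7% | 85.7% |
| 1.65 | 85.3% | 85.3% | 87.8% |
| 2.0 | 84.8% | 84.9% | 88.3% |

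A repeat gave about 88 to 89% with the covariate at odds ratios of 1.65 to 2.0.

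**The case against.** The strongest reply is that the behavioral wording is leftover text with one obvious reading. The primary objective, the Analysis of Primary Outcome paragraph and the sample size section all fix the contrast as adaptive versus standard. A reader might infer from Section 13.4 that the primary test cannot be run as written. The documents do not support that: a one-level factor drops out and the contrast remains. This part of the objection stands. The wording is still wrong, and it appears in two places.

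On the stratum, the protocol is silent and does not exclude it, and stratum terms are often left to the statistical analysis plan, which is not at hand. Silence alone would be no finding. It counts here because the sentence does list factors, and lists the wrong ones. The lack of numerical consequence is conceded.

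On the covariate rule, the row is exploratory, it defers to Section 13, and Section 13 does not repeat it. A reader might infer that the rule inflates type I error. The simulations do not show that for the selected model. The 6.1% arises only if the better of two models could be reported, which the protocol does not propose. What remains is that the row's wording reaches the primary outcome and nothing in Section 13 says otherwise.

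A reader might also count it an error that baseline cigarettes per day and FTND are not in the model. It is not: an unadjusted randomized comparison is valid, and the gain rests on an assumed odds ratio.

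**Conclusion.** The point holds as a mismatch between the stated model and the design, together with a primary model that is not fixed in advance. Confidence is high for the behavioral term, which is a plain contradiction within the protocol. The stratum and covariate points are weaker: one is an omission by silence, the other an exploratory-table phrase with wider reach than its label.

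The effect on validity is small. Type I error is about 5%, and power is about 86% with or without the stratum term. These figures rest on the protocol's assumed abstinence rates and an equal split of medication choice. The figure of about 88 to 89% with a baseline covariate also rests on an odds ratio of 1.65 to 2.0 per SD that the documents do not supply. The sample size does not need to change.

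**What to change.** - In Section 13.4 (Statistical Hypothesis, Model, and Method of Analysis), delete the reference to behavioral groups. In Section 3.6, delete the matching reference to behavioral treatments in the sample size sentence.
- State one primary model in Section 13.4: logistic (binomial) regression of biochemically confirmed 30-day abstinence at 12 weeks on adaptive versus standard, with chosen medication (varenicline or patch) as a stratum term.
- In Section 6, remove the significance condition for the primary outcome. Name in advance any baseline covariates to be used. Baseline cigarettes per day, FTND, or both are already collected and are an optional gain in efficiency, not the correction of an error.

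The cost is a few lines of analysis wording, to be settled before outcomes are examined by arm and carried into any statistical analysis plan. Data collection, sample size and trial conduct are unchanged.

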| Secondary   | To compare 7-day point prevalent biochemically confirmed abstinence rates at 2- and 12-weeks post-TQD in participants randomized to adaptive pharmacotherapy algorithm vs. standard-of-care treatment.                                                                                                                                            | Biochemically confirmed 2-week and 12-week post-TQD 7-day point prevalence abstinence.

This includes Carbon Monoxide Breath Testing < 7 ppm and a 7 day diary of cigarette use completed prior to in-person visits.                                                                                                                                                                                            | See Section 13 |
| Secondary   | To compare phone-based self-reported abstinence at multiple time points (1, 2, 6, 12, 26 and 52 weeks post-TQD) assessed by phone in participants randomized to adaptive pharmacotherapy algorithm vs. standard-of-care treatment.                                                                                                                | Self-reported 7-day point abstinence rates via phone-based assessment at 24 hours post-TQD, 1-week post-TQD, 2-week post-TQD, 6-week post-TQD, 26-week post-TQD, and 52-week post-TQD.

This includes phone-based assessment of single-item question on smoking over the last 24 hours (for 24-hour and 1-week phone call assessment time points) and over the last 30 days for 26-week to 52-week time points. | See Section 13 |
| Secondary   | To compare smoking reduction (number of cpd) at 2- and 12-weeks post-TQD in participants randomized to adaptive pharmacotherapy algorithm vs. standard-of-care treatment.                                                                                                                                                                         | Self-reported abstinence via diary correlated with biochemically-confirmed 2-week and 12-week post-TQD 7-day point prevalence abstinence.                                                                                                                                                                                                                                                                             | See Section 13 |

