## Appendix 19: Phone-Based Assessments

### Abstinence Status

1. Have you smoked any cigarettes in the last 24 hours? (Call 4)
2. How many cigarettes have you smoked in the last 24 hours? (Call 4)
3. Have you smoked cigarettes in the last 7 days? (Call 1,2,3, 4, 5, 6, 7, 8, 9, 10)
4. On average, how many cigarettes have you smoked per day in the 7 days week? (Call 1,2,3, 4, 5, 6, 7, 8, 9, 10)
5. Have you smoked cigarettes in the last 30 days? (Calls 7, 8, 9, 10 )
6. On average, how many cigarettes have you smoked per day over the last 30 days? (Calls 7, 8, 9, 10 )

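### Several secondary endpoint statements conflict: 30-day abstinence at week 2 reaches back 16 days before the quit day, and the confirmation, cigarettes-per-day, missing-data and phone-recall rules disagree between sections.

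*Protocol*

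**What the plan says.** Five parts of the protocol bear on the secondary smoking outcomes.

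- **(a) 30-day abstinence at week 2.** The secondary-outcomes paragraph of Section 13.4 (Statistical Hypothesis, Model, and Method of Analysis) lists "self-reported 7 and 30-day continuous abstinence and number of cigarettes smoked per day at 2- and 12-weeks post TQD". Section 3.6 repeats the pairing: "self-reported 7 and 30-day continuous abstinence at 2- and 12-weeks post-TQD".
- **(b) Confirmation.** Both of those texts rest on self-report. The objective in Section 13.2 reads "To compare 7-day point prevalent biochemically confirmed abstinence rates at 2- and 12-weeks post-TQD in participants randomized". Section 3.1 has the same objective, and Section 6 gives the instrument as CO below 7 ppm plus a 7-day diary.
- **(c) Smoking reduction.** In the Section 6 table, the objective on cpd at weeks 2 and 12 carries the endpoint "Self-reported abstinence via diary correlated with biochemically-confirmed 2-week and 12-week post-TQD 7-day point prevalence abstinence". The matching phone objective is given abstinence rates.
- **(d) Missing data.** Section 13.3 (Handling of missing values) says that "any subjects lost to follow-up after the point of randomization will be counted as non-abstinent", without limiting this to the primary outcome. Section 13.4 says: "Secondary smoking outcomes will be assessed using intent-to-treat principles with use of multiple imputation to account for missing data". Its multilevel-modelling paragraph, like Section 3.6, adds that non-abstinent coding will also be used for univariate outcomes.
- **(e) Phone recall.** Section 6 calls the phone endpoint 7-day abstinence. It then specifies 24-hour recall at the 24-hour and 1-week calls, "and over the last 30 days for 26-week to 52-week time points". Appendix 19 asks "Have you smoked cigarettes in the last 7 days? (Call 1,2,3, 4, 5, 6, 7, 8, 9, 10", that is, at every call.

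**The concern.** Section 6 sends each endpoint to Section 13 for its analysis, and the two then differ on what is measured, how it is confirmed and what happens to missing values. These are contradictions within the protocol, not detail left to a later plan.

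An analyst following the text literally would produce a week-2 comparison in which almost nobody can succeed. The same analyst would have to choose, possibly after seeing data, between confirmed and self-reported abstinence and between two missing-data rules. The phone objectives are to be compared across time points by multilevel modelling. If the recall window changes from 24 hours to 7 days to 30 days along the series, an apparent time trend is partly a change of definition.

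**Working it through.** The protocol states no figure on this point to reproduce. The check is calendar arithmetic with the TQD as day 0, a comparison of sections, and one illustration for missing data.

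**(a) Week-2 window.** Inputs: visit at day +14; a 30-day look-back (Appendix 11); pre-quit treatment of 28 days (Section 3.5).

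- Window opens at 14 − 30 = day −16, so 16 of its 30 days precede the quit day.
- To pass, a participant must have stopped by about 28 − 16 = 12 days after starting treatment. The response visit is 14 days after the start, so this is before the adaptive decision.
- At that time the adaptive arms are on active drug and the standard arms on placebo (Section 10.2). Any passes therefore reflect early pre-quit cessation, not the quit attempt or the added bupropion.
- At week 12 the window opens at 84 − 30 = day +54, wholly after the quit day, so 30-day abstinence is sound there.
- No objective in Section 6 or Section 13.2 asks for 30-day abstinence at week 2.

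**(b) Confirmation.** Sections 3.1, 6, 10.4 and 13.2 require biochemical confirmation of 7-day abstinence at weeks 2 and 12. Sections 3.6 and 13.4, which describe the secondary analysis, mention self-report only.

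**(c) Reduction.** The fault is confined to two endpoint cells in Section 6. Cpd is named as an outcome in Sections 3.6 and 13.4. It is collected by diary (Section 10.7.5), by clinic item (Appendix 11) and by phone (Section 10.7.6, Appendix 19).

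**(d) Missing data.** Inputs: planning rates of 39.7% adaptive and 23.4% standard (Sample Size Calculation), taken here as rates among completers. Loss rates are assumed, because the protocol gives none. With loss L in each arm, missing = smoking gives each arm rate × (1 − L). Imputation under missing at random leaves the completer difference at 39.7 − 23.4 = 16.3 points.

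| Loss, adaptive / standard | Adaptive | Standard | Difference (points) |
|---|---|---|---|
| 10% / 10% | 35.7% | 21.1% | 14.7 |
| 20% / 20% | 31.8% | 18.7% | 13.0 |
| 30% / 30% | 27.8% | 16.4% | 11.4 |
| 20% / 30% | 31.8% | 16.4% | 15.4 |
| 30% / 20% | 27.8% | 18.7% | 9.1 |

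Differences come from unrounded rates; for example 0.397 × 0.7 − 0.234 × 0.8 = 0.2779 − 0.1872 = 0.091. Section 10.6.3 says attrition is already inside the planning rates. On that reading, at 20% equal loss the imputed difference would be 16.3 / 0.8 = 20.4 points against 16.3, the same ratio as in the table.

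**(e) Phone recall.** The call timetable in Section 10.4 puts call 4 at 1 day, call 5 at 1 week and calls 7 to 10 at about 6, 12, 26 and 52 weeks after the TQD.

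| Item | Section 6 | Appendix 19 |
|---|---|---|
| 24-hour recall | 24-hour and 1-week calls | call 4 only |
| 7-day recall | label of the whole endpoint | all calls |
| 30-day recall | 26 to 52 weeks | calls 7 to 10 |

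The Section 6 phone endpoints also add a 24-hour call and omit the 12-week call that the objectives name. At call 4 a 7-day window has 7 − 1 = 6 pre-quit days, so that call does not belong in a 7-day series. From call 5 on, the 7-day window no longer reaches back before the TQD.

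**The case against.** The strongest reply is that most of the protocol is right and the faults are local. The objectives consistently specify confirmed 7-day abstinence, and one item in Section 3.1 pairs the windows correctly: 30-day at week 12, 7-day at weeks 2 and 12. The list in Section 13.4 says what the analysis will include, so it need not displace the confirmed endpoint. Non-abstinent coding is described as additional for univariate outcomes, so both analyses can coexist, and it assigns no value to cpd. The 7-day phone item exists at every call, and a 24-hour question one day after the quit day is sensible in itself.

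Much of this stands, and it rules out three stronger readings.

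- A reader might infer that 30-day abstinence at week 2 is impossible. The Appendix 11 item is a plain look-back and nothing obliges participants to smoke before the TQD, so a very early quitter could pass.
- A reader might infer that reduction will not be measured, or that its objectives cannot be answered. Cpd is both collected and named as an analysed outcome.
- A reader might set the fall in one arm's abstinence level (39.7% × 0.3 = 11.9 points at 30% loss) beside the planned 16.3-point effect. One is a level within an arm and the other a difference between arms. The difference itself moves by 1.6 to 4.9 points under equal losses of 10% to 30%.

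The reply does not remove the conflicts. The week-2 pairing appears twice, the confirmed visit endpoint is absent from the analysis text, the two table cells are wrong, no lead missing-data rule is named, and Section 6 contradicts the phone form.

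**Conclusion.** The concern holds as a set of contradictions to reconcile before analysis. Item (a) is near-degenerate and serves no listed objective. Items (b) and (c) are mismatches between objective, endpoint table and analysis text. Item (e) would confound definition with time if Section 6 were followed literally, although no text obliges the model to mix windows.

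Item (d) is a missing hierarchy. Which rule should lead is partly a matter of preference; leaving it open is not. Across the assumed scenarios, counting losses as smokers instead of imputing shrinks the 16.3-point difference by between 0.9 points (20% adaptive, 30% standard) and 7.2 points (30% adaptive, 20% standard). That could change a secondary result. These figures rest on assumed losses, on the planning rates as completer rates, and on missing at random for the imputed comparison. The primary endpoint is not affected: its window, confirmation and order of analyses are stated consistently.

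**What to change.** - **(a)** In Sections 3.6 and 13.4, limit 30-day abstinence to week 12.
- **(b)** State CO below 7 ppm plus the 7-day diary as the secondary abstinence endpoint at weeks 2 and 12, with self-report as supportive.
- **(c)** In the two Section 6 rows, name cpd: the diary or the 7-day clinic item at visits, and the 7-day cpd item by phone. Use the same 7-day item at baseline. The screening list in Section 10.1 includes the recent-smoking questionnaire but not the diary, so a diary-based change score should not be assumed available.
- **(d)** Name one lead rule for secondary abstinence and report the other as sensitivity. The primary's order in Section 13.4 (losses counted as non-abstinent, then multiple imputation) is a ready template. State the rule for cpd separately.
- **(e)** Use the 7-day phone item at weeks 1, 2, 6, 12, 26 and 52 in the multilevel model, restore the 12-week call in Section 6, and keep 30-day recall as supportive from week 6.

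The cost is wording, plus one changed lead analysis if missing = smoking is chosen for secondary abstinence. With the 7-day questionnaire item as the cpd baseline, no new data item is needed.
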